#### Support mothers

1. *Baseline:* Age, socio-economic status, education, employment status, religion, baseline breastfeeding knowledge and attitude, parity, previous breastfeeding.

2. *At end of support activity of each participant:* Activity log sheets, satisfaction with mother-to-mother support system.

3. *Year 1*: In-depth interviews with SMs.

#### Lactation experts

1. *Baseline:* age, socio-economic status, education, employment status, parity, previous breastfeeding.

2. *Month 6:* Satisfaction with the study experience.

### Data management and quality assurance

#### Training details

1. Professional lactation experts: Nurses recruited for professional support will have extensive training on breastfeeding in the WHO/UNICEF 20-hour course on breastfeeding as a minimum requirement. If not already certified as International lactation consultant, the nurse will be offered the exam to become certified. Once the trial is over, the lactation experts will help deliver structured training in breastfeeding for AUBMC and SGH nurses working in normal nursery, neonatal intensive care unit, delivery suite, maternity ward, and obstetric clinics. As such, we believe that investment in those experts will be cost-effective on the long run to help both sites achieve the “Baby-Friendly Hospital” status.

2. Recruiters: Two research assistants will be trained to approach and contact potential subjects at both sites. Training will entail familiarizing them with all necessary documentation, including enrollment and consent forms in a structured 2-hour workshop. They will be trained to consent mothers in accordance with the ethical principles of informed consent, and call them using a prepaid phone card. Instructions and demonstrations on how to use these cards will also be given during the same workshop.

3. Support mothers: Training of SMs will take place at AUBMC at an agreed upon time and place. One of 3 pediatricians -part of the research team- will conduct seven training workshops. Each workshop consists of two 2-hour sessions and will include a maximum of 10 SM participants. The first of the 2 sessions will be mainly theoretical. It will entail a brief overview of the mother-to-mother support program and training on the LOVE (listen observe validate empower/educate) method of support. In the second part of the first session, *breastfeeding basics* will be discussed, including advantages of breast milk and risks of formula; common culture-specific misconceptions will be addressed and proper technique of breastfeeding will be demonstrated using visual aid material. Breastfeeding trouble-shooting, and criteria for referral to appropriate medical services will also be emphasized. These criteria aim to identify mothers with medical conditions such as mastitis or breast abscess and postpartum depression or psychosis as well as infant medical conditions, such as hyperbilirubinemia and/or dehydration. During the second session, which will be largely practical, support mothers will be asked to review what they have learned through interactive discussions; they will engage in role playing of “*what if*” scenarios as necessary, including failure to breastfeed scenarios. For those specific cases, SM’s empathy and positive attitude will be emphasized. They will subsequently be handed a small manual containing a list of local breastfeeding resources as well as their telephone log sheets and activity records.

#### Process evaluation

During the support period, an ongoing evaluation process will take place in order to identify potential problems and implement changes accordingly. The process evaluation will ensure that the intervention is delivered and implemented as planned by evaluating the dose delivered, dose received, and reached.

The study research assistant will contact BFMis and SMs bi-weekly to inquire about the support process, including address potential complaints. The inquiry findings will be shared with the principal investigator within one business day. Process amendments and/or improvements will take place within the same week if necessary. In case of a perceived need for referral by SMs, physician members of the research team will be notified within the same day and will contact the BFMi-SM pair in question to evaluate and confirm the medical urgency and refer-or not- accordingly. At the end of the support period, all records are returned to the research team. When the latter receives the records, a post-support survey is sent to the breastfeeding mother to fill and return for data entry and analysis. Separate surveys will be sent to each support mother and to the professional nurses to assess their satisfaction. All BFMis will be contacted by the research team on yearly basis for 5 years after the trial ends to ask about their success in breastfeeding future babies. In addition, all mothers in the control group will be contacted by the research team at 1 month, 3 months and 6 months after delivery for data collection and outcome assessment similar to the intervention group. They will also be contacted on yearly basis for 5 years after the trial ends to ask about their success in breastfeeding future babies.

### Sample size

The most recently reported 6-month exclusive breastfeeding rate in Lebanon is 2% [23], which is the expected rate in the control group. The complex intervention is hypothesized to increase the 6-month exclusivity rate in the intervention group to 12%. To detect this 10% difference between the two groups with 90% power and 5% type I error, 155 mothers are needed per group. Allowing for a loss-to-follow up rate of 30%, the needed sample size becomes 443 women. The number of SMs to be recruited is 74, assuming that each support mother will pair with 3 breastfeeding mothers from the intervention group.

### Statistical methods

We will compare continuous variables using Student’s *t* test and categorical variables using Chi square test. The relationship between breastfeeding exclusivity as outcome and the independent variables (maternal age, study group, socio-economic status, maternal education, study site, pediatrician’s gender, type of delivery, baby’s gender, parity, previous breastfeeding, maternal employment, mother’s religion, baseline breastfeeding knowledge and attitude, baseline social support) will be explored in bivariate and multivariate analysis. Regression models will be built to adjust for possible confounding in the relationship between the dependent and the independent variables stated above. All analysis will be done on intention to treat basis. The Statistical Package for Social Sciences (SPSS) will be used for data management and analyses. A p-value of <0.05 will indicate statistical significance.

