### Data collection

#### Participant mothers

1. *Baseline:* Age, socio-economic status, education, employment status, mother’s religion, baseline breastfeeding knowledge and attitude, parity, previous breastfeeding, baseline social support, study site, residence.

2. *Month 1:* Baby’s gender, mode of delivery, pediatrician’s gender, first feed at hospital, rooming in, breastfeeding status, baby’s illness visits (number, diagnosis, money spent on medicine and doctor’s fees), baby’s hospitalizations (number, diagnosis, cost), days lost from work due to baby’s illness, days lost from work due to mother’s illness, cost of formula feeds/week, cost of water used to prepare formula/week, mother’s non-routine doctor visits due to breastfeeding, cost of infant food/week, QoL.

3. *Month 3:* Breastfeeding status, baby’s illness visits (number, diagnosis, money spent on medicine and doctor’s fees), baby’s hospitalizations (number, diagnosis, cost), days lost from work due to baby’s illness, days lost from work due to mother’s illness, cost of formula feeds/week, cost of water used to prepare formula/week, mother’s non-routine doctor visits due to breastfeeding, cost of infant food/week, QoL.

4. *Month 6:* Breastfeeding status, baby’s illness visits (number, diagnosis, money spent on medicine and doctor’s fees), baby’s hospitalizations (number, diagnosis, cost), days lost from work due to baby’s illness, days lost from work due to mother’s illness, cost of formula feeds/week, cost of water used to prepare formula/week, mother’s non-routine doctor visits due to breastfeeding, cost of infant food/week, QoL, satisfaction of mother with mother-to-mother support system, breastfeeding knowledge and attitude of mother, in-depth interviews with BFMis.

5. *Year 1:* Breastfeeding status, baby’s illness visits (number, diagnosis, money spent on medicine and doctor’s fees), baby’s hospitalizations (number, diagnosis, cost), days lost from work due to baby’s illness, days lost from work due to mother’s illness, cost of formula feeds/week, cost of water used to prepare formula/week, mother’s non-routine doctor visits due to breastfeeding, cost of infant food/week.

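### The adjusted analysis of exclusive breastfeeding includes two variables that arise after randomisation and, if all listed terms enter one model, has only about 1.6 expected events per term

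*Protocol article*

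**What the plan says.** The Statistical methods section plans Student's t test for continuous variables and the chi-square test for categorical ones. It then names breastfeeding exclusivity as the outcome and gives one undivided list of 14 independent variables. Besides study group these are 13 covariates: the mother's age, education, employment, religion, parity and socio-economic status; previous breastfeeding; knowledge and attitude at baseline; social support at baseline; study site; and, in the middle of the list, "pediatrician’s gender, type of delivery, baby’s gender, parity, previous breastfeeding". The list is to be explored in bivariate and multivariate analysis, after which: "Regression models will be built to adjust for possible confounding in the relationship between the dependent and the independent variables stated above".

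Under Data collection, the Participant mothers schedule places these items at Month 1: "mode of delivery, pediatrician’s gender, first feed at hospital, rooming in, breastfeeding status". Women enter the trial in the first or second trimester (Study population), and the intervention begins in pregnancy (Intervention group).

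The planning figures are in Sample size: "The most recently reported 6-month exclusive breastfeeding rate in Lebanon is 2% [23], which is the expected rate in the control group", 12% in the intervention group, and "with 90% power and 5% type I error, 155 mothers are needed per group".

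**The concern.** Randomisation deals with confounding of the group comparison. Covariate adjustment in a trial is useful for precision, and it is safe when the covariates precede allocation. Two listed covariates do not meet that condition. Delivery type and the pediatrician's gender are recorded only after delivery, while allocation and the prenatal part of the intervention come months earlier. The Background reports Caesarean birth and male pediatrician as predictors of low breastfeeding. If either responds to the intervention, adjusting for it takes out part of the effect or opens a path to bias.

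The second issue is sparsity. The outcome is expected to be rare, and maximum-likelihood logistic regression with very few events per term gives odds ratios that are too far from 1. Here that error favours the intervention. Since the section does not rank its analyses, the inflated figure could be reported as the treatment effect.

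**Working it through.** **Inputs (Sample size section unless noted).** Control 2%; intervention 12%; power 90%; type I error 5%; 155 per group; 30% loss; 443 in total; 14 independent variables (Statistical methods).

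**1. The plan's own figure.** Two-sided test of two proportions with mean rate 0.07:

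n = [1.96·√(2·0.07·0.93) + 1.2816·√(0.02·0.98 + 0.12·0.88)]² / 0.10² = (0.707 + 0.453)² / 0.01 ≈ 134.7, so 135.

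With continuity correction: (134.7/4)·[1 + √(1 + 4/(134.7·0.10))]² ≈ 154.1, so 155. This matches. The total also matches: 310/0.70 = 442.9, so 443.

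**2. Expected events.**
- 310 completers: 155·0.02 + 155·0.12 = 3.1 + 18.6 = 21.7. Per term: 21.7/14 = 1.55.
- All 443 observed: 443·0.07 = 31.0. Per term: 2.2.
- Control rate of 4.1% to 10.1% (the range in the Background) with the 10-point difference kept (an assumption): 155·(0.041 + 0.141) = 28.2 to 155·(0.101 + 0.201) = 46.8. Per term: 2.0 to 3.3.

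Fourteen is the minimum number of terms, because socio-economic status, education and religion may need several levels each.

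**3. Effect on the odds ratio.** The true marginal odds ratio is (0.12/0.88)/(0.02/0.98) = 6.68. Maximum-likelihood logistic regression was simulated with 1,500 data sets per row. Seven covariates were binary and six normal, and data sets without a finite estimate were excluded. The prognostic rows assume a log odds ratio of 0.25 per standard deviation for each covariate. Their true value is the conditional odds ratio, which is larger because odds ratios are not collapsible.

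| Per arm | Covariates | True OR | Median, none fitted | Median, 13 fitted | 13 fitted vs true |
|---|---|---|---|---|---|
| 155 | unrelated to outcome | 6.68 | 6.66 | 7.66 | +15% |
| 155 | modestly prognostic | 7.37 | 6.92 | 9.05 | +23% |
| 221 | unrelated to outcome | 6.68 | 6.92 | 7.43 | +11% |
| 221 | modestly prognostic | 7.37 | 6.79 | 8.37 | +14% |

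With so few control events the medians are coarse. In the third row the unadjusted median is itself above 6.68, so the 13 covariates account for about 7.43/6.92 = 1.07 there. With one covariate unrelated to outcome at 155 per arm (800 data sets), the median was 6.89, against 6.91 with none in the same data, so a small model adds no visible inflation.

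**4. Other properties.** Type I error stayed near 5%. Coverage of the 95% interval was about 97% to 98% in fits that converged. About 4% of data sets at 155 per arm gave no finite estimate. That is the probability of no control events, 0.98^155 = 0.044, and the rate was essentially the same with no covariates.

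**5. Timing.** Setting the Month 1 items against the list of independent variables gives three overlaps: delivery type, the pediatrician's gender and the baby's gender. The baby's gender is determined before enrolment and is only recorded late, so it cannot be affected by allocation. The other two are not recorded before Month 1.

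**The case against.** The strongest reply is that the primary comparison is untouched. The main outcome is a difference in rates, a chi-square test is planned for categorical variables, and the sample size reproduces as a two-proportion calculation. That stands, and a reader who infers that the trial's main test is compromised goes beyond the document. What remains is that the section does not rank the chi-square result above the adjusted one.

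The second reply is that one 14-term logistic model is an inference. The text speaks of exploring and of models in the plural, and names neither logistic regression nor an odds ratio. This also stands, so the inflation figures are conditional. But the sentence on confounding refers to the whole list and gives no rule for reducing it.

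The third is that the distortion is modest relative to the uncertainty. The standard error of the unadjusted log odds ratio is √(1/3.1 + 1/151.9 + 1/18.6 + 1/136.4) ≈ 0.62. The shift ln(7.66/6.68) ≈ 0.14 is about a fifth of that. This is fair and bears on severity.

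Some stronger readings are tempting but are not supported:
- That the intervention does change delivery type or choice of pediatrician. The documents do not show this; the class content in Appendix-A concerns breastfeeding only. A woman with earlier children may already have a pediatrician. The path is possible, not demonstrated.
- That the baby's gender belongs with the post-randomisation variables. It does not.
- That adjustment can only add bias. Study site is the stratification factor, and previous breastfeeding is a sensible baseline covariate.
- That the covariates cause the failed fits. Empty control cells cause them.
- That the inflation is 30%. That requires about 20 terms, a number the document does not give.

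**Conclusion.** The point holds in limited form and should be fixed. The covariate list for the adjusted effect includes two variables that arise after randomisation and that the article itself reports as predictors of the outcome. Adjusting for them carries a risk of bias that cannot be sized from the documents, and randomisation makes it unnecessary. If the whole list is fitted in one logistic model, there are about 22 events for 14 terms and the odds ratio is inflated by about 15%, or 11% to 23% across the scenarios examined. Those figures rest on the planning rates, maximum-likelihood fitting and assumed covariate distributions and strengths. The harm is to the adjusted estimate, not to the chi-square comparison or the error rate.

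**What to change.** In Statistical methods:
- Name the chi-square comparison, reported as the difference in 6-month exclusivity rates, as the primary analysis.
- Limit the adjusted treatment-effect model to study group, study site and one or two prespecified covariates fixed before randomisation, such as previous breastfeeding. Fit it with Firth penalisation, which also gives an estimate when a control cell is empty, or report a standardised risk difference, which matches the definition of the main outcome.
- Exclude type of delivery and the pediatrician's gender from every model that estimates the treatment effect. The baby's gender need be dropped only to save a term.
- Keep the full list for a separately labelled exploratory analysis of predictors of exclusive breastfeeding.

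If knowledge and attitude is considered as a covariate, first settle when it is measured. The section on prenatal education collects it at antenatal sessions that follow enrolment and are open only to the intervention group, whereas the Participant mothers schedule lists it as baseline.

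The change is wording and needs no new data. The cost is less covariate adjustment in the effect model.

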### Cost analysis

The economic efficiency of breastfeeding promotion will be investigated through the assessment of the costs incurred during 1 year by families feeding their infants artificial milk versus breastfeeding (whether exclusive or mixed). The analysis will take into consideration the cost of planning and implementing the Complex Intervention for Breastfeeding Promotion initiative and the various costs associated with healthcare provision, nutrition and lost productivity during one year for families in both study groups. The cost analysis will test whether the economic burden of exclusive breastfeeding is less than partial breastfeeding, and less than formula feeding at the family level, as well as at the national level. We will explore the association between the infant feeding status (exclusive breastfeeding, partial breastfeeding, formula feeding), and study group (intervention/control) as independent variables, and the following dependent variables: non routine doctor visits, hospitalization, work absences due to infant sickness, work absences due to mother sickness, cost of formula milk, cost of water used for formula preparation, mother’s non-routine doctor visits related to breastfeeding, lost productivity of parents due to breastfeeding, and cost of other infant foods.

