### Secondary outcome measures

Differences between the two groups with respect to the following:

a) Breastfeeding exclusivity rates at 1 and 3 months.

b) Breastfeeding rates (exclusive or mixed feeding) at 1, 3 and 6 months.

c) Breastfeeding knowledge and attitudes of mothers at 6 months.

d) Success of a mother-to-mother support system measured as satisfaction rates of BFMis, SMs, and lactation experts; BFMi referral rates and adverse events during the 6 months.

e) Cost-benefit and cost-effectiveness analyses of the complex intervention.

f) Maternal quality of life at 1, 3 and 6 months using the validated Postpartum Quality of Life (QoL) questionnaire [30].

g) Success of mothers in exclusively breastfeeding new babies, measured as the percent difference between the intervention and control groups in 6-month breastfeeding exclusivity rates of subsequent babies, up to 5 years following the intervention.

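### The economic analysis is framed and tested by achieved feeding status, although the stated outcome is the cost-effectiveness of the randomised intervention; one listed cost variable has no matching data item

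*Protocol article*

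**What the plan says.** The protocol article introduces its secondary outcomes as "Differences between the two groups with respect to the following", and item (e) reads "Cost-benefit and cost-effectiveness analyses of the complex intervention". Associated studies assigns the same task to Sub-study 7. Statistical methods states that every analysis follows intention to treat.

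The Cost analysis section opens with a different comparison: one-year costs of families giving artificial milk against those of families who breastfeed, exclusively or not. Its one stated hypothesis is: "The cost analysis will test whether the economic burden of exclusive breastfeeding is less than partial breastfeeding, and less than formula feeding". It then names infant feeding status in three categories "and study group (intervention/control) as independent variables, and the following dependent variables", followed by nine cost and resource variables. The last two are "lost productivity of parents due to breastfeeding, and cost of other infant foods".

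The section also says that programme cost will be taken into account, together with healthcare, nutrition and "lost productivity during one year for families in both study groups". It states no between-arm difference in total cost and no cost per additional exclusively breastfed infant.

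For month 1 to year 2, Data collection lists work days lost to illness of the baby or of the mother. For years 3 to 5 it lists only those lost to the baby's illness.

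**The concern.** Outcome (e) asks what the intervention costs and saves compared with standard care. Only a comparison by allocated arm answers that with the protection of randomisation. Families grouped by achieved feeding differ in other ways. The Background itself reports that lower socio-economic status, Caesarean birth, urban residence and early discharge predict low breastfeeding, and these may also bear on healthcare use and cost. Reverse causation is plausible too: the Background reports a belief that milk is harmful when the mother is ill, so illness may end breastfeeding and also generate the doctor visits and absences counted as outcomes. Statistical methods lists adjustment covariates for exclusivity as the outcome; Cost analysis names none for costs.

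If feeding status and study group enter one model, the group coefficient no longer measures the total effect of allocation, because feeding is a pathway by which the intervention would change family costs.

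At stake is a secondary outcome that the Discussion hopes will support replication elsewhere. A saving seen between feeding groups could be read as the saving produced by the programme, which is a different and probably much smaller quantity.

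**Working it through.** **Planning figures.** Cost analysis gives no figure of its own. Sample size gives 2% and 12% exclusive at 6 months, 90% power, 5% type I error, 155 per group and 443 in total after 30% loss. These reproduce. The two-sided pooled formula gives 135 per group without continuity correction and 155 with it; 2 × 155 = 310, and 310 / 0.70 = 442.9, so 443. Nothing below changes these numbers.

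**By arm against by feeding.** The documents give no costs, so let C be an assumed saving in family cost per infant exclusively breastfed at 6 months, and P the programme cost per intervention woman.

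- By-arm difference in family cost: (0.12 − 0.02) × C = 0.10 C, before programme cost.
- By-feeding contrast without confounding: 1.0 C, which is 1.0 / 0.10 = 10 times as large.
- Incremental cost per additional exclusively breastfed infant: (P − 0.10 C) / 0.10 = 10 P − C. On family costs alone the programme breaks even only if P is at most 0.10 C. The by-feeding contrast cannot show this, because P attaches to allocation and not to feeding.

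**Confounding and the joint model.** An illustrative simulation used 2,000,000 women, 1:1 allocation and the 2% and 12% rates. An unmeasured standard normal trait has correlation 0.5 with the latent tendency to breastfeed exclusively, and lowers cost by k per standard deviation. Residual cost noise has standard deviation 1 C. The whole intervention effect is assumed to run through exclusivity. Results are in units of C:

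| k (assumed) | By arm | By feeding | Study-group coefficient, feeding status in the model |
|---|---|---|---|
| 0 | −0.102 | −1.005 | 0.000 |
| 0.25 | −0.100 | −1.235 | +0.025 |
| 0.5 | −0.101 | −1.475 | +0.048 |
| 1.0 | −0.100 | −1.955 | +0.099 |

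The by-arm contrast stays at about −0.10 C throughout. The by-feeding contrast grows with confounding. The jointly modelled group coefficient is zero or has the opposite sign to the true by-arm effect, because at a given feeding status the control women are the more favourably selected ones.

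**Collinearity.** Expected exclusive breastfeeders are 155 × 0.02 = 3.1 and 155 × 0.12 = 18.6, and 18.6 / 21.7 = 86% are in one arm. The correlation of arm with exclusivity is nevertheless small. The overall rate is 0.07, the standard deviation is √(0.07 × 0.93) = 0.255, and the covariance is 0.25 × 0.10 = 0.025, so r = 0.025 / (0.5 × 0.255) = 0.20. Variance inflation is 1 / (1 − 0.20²) = 1.04. Collinearity is not the problem.

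**Data item.** Setting Cost analysis beside Data collection, the listed illness absences, doctor visits and costs of formula, water and infant food have counterparts. Parental productivity lost because of breastfeeding does not: the only work-time items concern illness. If such a loss occurs, it falls on breastfeeding families, and leaving it out favours breastfeeding.

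**The case against.** The strongest reply is that the section already takes in programme cost and family costs in both groups, under a between-group outcome heading and an intention-to-treat statement. That stands as far as the data go. A reader might infer that the trial cannot estimate cost-effectiveness, but the documents do not support this: a by-arm comparison is feasible, and only the stated comparison and test point elsewhere.

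A reader might also infer that the randomised contrast will be adjusted away. The text speaks only of exploring associations with the two independent variables and does not specify a joint model. Separate by-group associations remain a fair reading, since Statistical methods plans both bivariate and multivariate work for exclusivity. Even with a joint model, a coefficient of exactly zero needs full mediation through feeding. Home visits, the hotline and referral could change mothers' doctor visits directly.

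The 86% figure might suggest that arm and feeding status are too entangled to separate; a variance inflation of 1.04 shows otherwise. Nor does any passage show that breastfeeding-related productivity loss is the main cost to families.

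Finally, an article may leave model specification, interval methods and the detail of the incremental ratio to the Sub-study 7 plan, and comparing the burden of feeding modes is a legitimate question in itself. Both are granted. The point concerns the comparison that the article does state, which does not match its own outcome.

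**Conclusion.** The point holds as a mismatch between a stated secondary outcome and the analysis stated for it. Outcome (e) and intention to treat call for a contrast by allocated arm; the framing sentence and the only hypothesis test in Cost analysis use a post-randomisation, non-randomised one. At the protocol's own rates the two differ by a factor of 10 without confounding, and by more if women who breastfeed exclusively would have had lower costs anyway. That factor rests on an assumed saving that operates only through 6-month exclusivity. C and k are assumptions, and the documents give no planning rates for partial versus formula feeding. The joint-model problem is conditional on a natural but not explicit reading. The missing data item is a separate, plain inconsistency. Neither affects the primary outcome or the sample size, but both should be corrected.

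**What to change.** 1. State as the main economic analysis the one-year comparison of mean total cost per woman by allocated arm, programme cost included, with its uncertainty, and the incremental cost per additional infant exclusively breastfed at 6 months. Feeding status should not be in this model.
2. Keep the exclusive, partial and formula comparison, labelled secondary and observational, adjusted for baseline socio-economic status, education and employment, all of which are already collected. State that it does not estimate the effect of the intervention.
3. Add one item on work time lost because of breastfeeding to the month 1, 3, 6 and year 1 forms, or remove that variable from the Cost analysis list.

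The cost is a few sentences of analysis text and at most one question on existing forms. No extra contacts or participants are needed.
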